### **13.7.3 Global Evaluation of Tolerability by the Subjects and Investigators**

The subjects and the investigators will evaluate independently the tolerability of the IP by means of a global scaled evaluation with "very good", "good", "moderate" and "poor".

## **13.8 STUDY DISCONTINUATION**

Subjects may withdraw their consent and discontinue their participation in the clinical study at any time, without giving a reason for discontinuation. The investigator may terminate the clinical investigation for single subjects. Further, the sponsor has the right to terminate this clinical investigation.

### **13.8.1 Withdrawal of Subjects**

Reasons for subject's withdrawal may be for example:

- Serious adverse event (SAE)

- Intolerance of the investigational product
- Required additional therapy due to other complaints, which could influence the safety of the subject or the results of the study
- Clinically significant illness or intake of concurrent medication according to exclusion criteria, which could influence the results of the study
- Subject is not compliant with study requirements (according to investigator judgement)
- Withdrawal of informed consent
- Subjects in the study once the number of treated subjects has been completed

Reason, time and specific details of a subject's withdrawal are documented in the CRF. Each subject terminating the study prematurely will be asked to undergo the end-of-study visit, to be documented in the CRF, as follows:

- In case the subject has already completed visit 2, the end-of-study visit would correspond to Visit 3,
- In case the subject has not completed visit 2, the end-of-study visit would correspond to the Termination Visit. Subject not fulfilling criteria for continuation at V2 will complete the TV.

If possible, the IP should be returned by the subject. Subjects who discontinue due to safety reasons should, whenever possible, be seen and assessed by the investigator and be medically advised as appropriate.

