### 13.3 VISIT FOR SUBJECTS WITHOUT SYMPTOMS DURING THE STUDY PERIOD: TERMINATION VISIT (TV), 16 WEEKS $\pm$ 7 DAYS AFTER V1

- Questioning and documentation of possible occurrence of AEs
- Questioning and documentation of new or changed concomitant treatment
- Return of the subject diary
- Return of IP

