## **13.7 ASSESSMENT OF SAFETY**

### **13.7.1 Blood Pressure and Pulse Rate**

Sitting blood pressure and pulse rate will be measured using standard products and procedures at all study visits.

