#### **14.2.2 Documenting and Reporting Device Deficiencies and Incidents by the Investigator**

During all examinations after applying the investigational product, the subjects will be asked about any device deficiencies observed. If a device deficiency is reported, the deficiency including the assessment if it may be regarded as an incident will be recorded in the study documentation.

Reportable are all device deficiencies that might have led to a serious adverse event if

- a) suitable action had not been taken, or
- b) intervention had not been made or
- c) if circumstances had been less fortunate,

as well as any incidents.

The reporting is handled under the SAE reporting system and will be reported as specified in the form "Report on device deficiencies" (*"Bericht über Mangel des Medizinproduktes / Vorkommnis"*, in the ISF) immediately after becoming aware (not later than 3 calendar days) to the sponsor and the CRO.

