#### 15.12 ANALYSIS OF SAFETY ENDPOINTS

All subjects treated at least once with the IP will be used to evaluate issues of tolerability and safety. Safety evaluations will be based on assessment of adverse events, the global evaluation of tolerability by subject and investigator, physical examination, vital signs, and assessment of adverse device effects and reporting of device deficiencies.

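### Section 13.8.1 picks the end-of-study visit by V2 completion, not product use, so treated subjects who withdraw before V2 have no scheduled post-use examination or tolerability rating

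*Protocol*

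**What the plan says.** Protocol Section 13.8.1 asks each subject who stops early to attend an end-of-study visit. If V2 has been completed, that visit is V3. Otherwise, "In case the subject has not completed visit 2, the end-of-study visit would correspond to the Termination Visit". A further sentence adds: "Subject not fulfilling criteria for continuation at V2 will complete the TV". Neither sentence mentions whether IP was used.

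The visit so assigned is defined in Section 13.3 under the heading "VISIT FOR SUBJECTS WITHOUT SYMPTOMS DURING THE STUDY PERIOD: TERMINATION VISIT (TV), 16 WEEKS". It has four items: adverse-event questioning, concomitant treatment, return of the diary and return of IP. The flow chart in Section 22.2.2 agrees. Its rows for device deficiencies and global evaluation are empty, and those for physical examination and for blood pressure and pulse are marked at V1 only.

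On the analysis side, Section 15.12 states: "All subjects treated at least once with the IP will be used to evaluate issues of tolerability and safety". Section 15.5 defines the treated set by receipt of at least one dose. Section 8.4 lists five safety endpoints: physical examination, vital signs, global tolerability at the end of the study, adverse events, and device deficiencies at V2 and V3.

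**The concern.** Whether a subject belongs to the safety analysis depends on IP use. Which assessments a withdrawing subject receives depends on V2. The two do not coincide, because IP starts once the symptom conditions of Section 11.3 are met, while V2 follows 1 to 3 days later and may be put off over a weekend or holiday (Section 13.6.2). A subject who takes a few doses, dislikes the spray and withdraws in that interval is treated for the analysis but handled as untreated at the final visit.

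Section 13.8.1 itself lists intolerance of the product as a reason for withdrawal, and Section 7.2 warns of coughing and hoarseness if the spray is inhaled. Withdrawal after the first doses is therefore foreseeable, and those who do so may differ in tolerability from those who stay. A rating or examination that was never recorded cannot be recovered by any analysis plan, so this has to be settled in the protocol.

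**Working it through.** No arithmetic applies. The protocol gives no rate of withdrawal between first dose and V2, and the sample size of 169 per group does not enter. The check is a comparison of texts.

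**Step 1: can a treated subject reach the TV without V2?** Yes. Under Section 11.3 use begins at symptom onset; under the Synopsis visit schedule V2 comes 1 to 3 days after onset and first use. Withdrawal between the two leads to the TV.

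**Step 2: item by item for that subject.**

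| Item | V3 (13.2.2, 22.2.1) | TV (13.3, 22.2.2) | Other text | Result |
|---|---|---|---|---|
| Adverse events | Yes | Yes | 14.2.1: all examinations | Covered |
| Physical examination | Yes | No | Synopsis: V1, V2, V3. 13.8.1: safety withdrawals are seen and assessed where possible, content not stated | Gap |
| Global tolerability | Yes | No | 8.4: at study end. 13.7.3: no visit named. Synopsis: V3 | Gap |
| Vital signs | Yes | No | 13.7.1: every visit. Synopsis: V1, V2, V3 | Conflict |
| Device deficiencies | Yes | No | 14.2.2: every examination after use. Synopsis and 8.4: V2 and V3 | Conflict |
| IP accountability | Return and accountability | Return only | 11.5 and 11.9.1: returned IP is weighed, with no visit named | Wording only |

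**Step 3: the two conflicts.** Section 13.7.1 says blood pressure and pulse "will be measured using standard products and procedures at all study visits". The TV is a study visit, yet neither its list nor its flow chart includes them. Section 14.2.2 says "During all examinations after applying the investigational product, the subjects will be asked about any device deficiencies observed". Whether this reaches the TV depends on whether a visit with no physical examination counts as an examination. At Section 13.3 the corresponding item reads only "Questioning and documentation of possible occurrence of AEs", whereas the V2 and V3 lists add device deficiencies. Site staff working from the visit list would omit both; staff working from the general rules would do both.

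**Step 4: subjects who attend V2 but do not continue.** Section 13.2.1 schedules examination, vital signs, adverse events and device deficiencies at V2. A treated subject who stops there already has post-use data on these and mainly lacks the tolerability rating. The criterion in Section 10.3 is a V2 after symptom onset and start of IP by the predefined rules, so some who fail it may never have used IP. For them the TV is suitable.

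**The case against.** The best reply is that little is lost. General rules already call for vital signs, deficiency questioning and weighing of returned IP. Adverse events are asked about at the TV, with intensity and relationship to IP (Section 14.2.1). The reason, time and details of withdrawal go into the case report form, and safety withdrawals are to be seen by the investigator where possible. Reportable deficiencies must be notified within 3 calendar days, independent of any visit (Section 14.2.2). The group is narrow: stopping the spray is not leaving the study, so the subject must withdraw within a few days of the first dose and still attend a final visit that is only requested. All of this stands, and it limits the point.

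A reader might go further in three ways, none of which the documents support.

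- That all these data are never scheduled for early leavers. This is true only of the post-use examination and the tolerability rating. For vital signs and deficiencies the protocol contradicts itself, and accountability is largely provided for.
- That intolerance or a faulty spray would go unseen and the safety summaries would look too favourable. An intolerance case would still appear as an adverse event and as a withdrawal reason, and a deficiency that causes an adverse event enters that evaluation (Section 15.12). The direction and size of any distortion are unknown.
- That the number affected can be found by applying a rate to the 400 planned subjects. No rate is given, and the Synopsis and Section 15.4 define the 400 as completing V2 and V3, which excludes anyone who leaves before V2.

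The reply does not close the two gaps. The provision for safety withdrawals names no endpoint assessment and covers only those subjects. Tolerability is set for study end, but every schedule places it at V3.

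**Conclusion.** The point holds in limited form. Subjects who used IP and withdrew before V2 belong to the safety analysis, but the visit assigned to them schedules neither a post-use physical examination nor the global tolerability rating. For vital signs and device deficiencies the protocol contradicts itself and the passages must be reconciled.

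The size cannot be computed from the document. It is probably small, because the interval between first dose and V2 is normally 1 to 3 days. The effect is confined to descriptive safety tables; no efficacy result is touched and the core adverse-event data are kept. The conclusion assumes that sites follow the visit lists and flow charts as written, and that some subjects do withdraw in that interval and attend the final visit.

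**What to change.** In Section 13.8.1, choose the end-of-study visit by IP use. Any withdrawing subject who has used at least one dose, whether or not V2 took place, has the existing V3 safety assessments recorded: device deficiencies, physical examination, vital signs, global tolerability and IP accountability. Keep the TV for subjects who never used IP. Apply the same rule to the sentence on subjects who do not continue at V2.

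Then reconcile Section 13.3 and flow chart 22.2.2 with Sections 13.7.1, 14.2.2 and 15.12, so that the visit lists and the general rules ask for the same things, and use the same accountability wording as Section 11.5.

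The cost is a sentence in Section 13.8.1, matching edits in Section 13.3 and the flow chart, and use of the V3 assessments already in the protocol. The only downside is a slightly longer final visit for a few subjects. Subjects who decline the visit will still contribute nothing, under either rule.

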### **13.8.2 Study Discontinuation Criteria**

If the clinical investigation has to be discontinued, each subject is to be treated as described above.

The sponsor has the right to terminate this clinical investigation, e.g. for the following reasons:

- Serious, insolvable problems with the quality of the data
- Unforeseeable circumstances at the investigational sites, which require discontinuation of the study (at an individual site and/or in general)
- Unacceptable risks
- New scientific or medical knowledge

## **14 SAFETY EVALUATION AND REPORTING**

### **14.1 DEFINITIONS**

#### **14.1.1 Adverse Event (AE)**

Any untoward medical occurrence, unintended disease or injury, or any untoward clinical signs (including an abnormal laboratory finding) in subjects, users or other persons, whether or not related to the investigational medical device.

This includes events related to the investigational device or the comparator and those related to the procedures involved.

For users or other persons this is restricted to events related to the investigational medical device.

#### **14.1.2 Adverse Device Effect (ADE)**

Adverse event related to the use of an investigational medical device.

This definition includes adverse events resulting from insufficiencies or inadequacies in the instructions for use, the deployment, the implantation, the installation, the operation, or any malfunction of the investigational medical device.

This includes any event that is a result of a use error or intentional misuse.

#### **14.1.3 Device Deficiency**

Inadequacy of a medical device with respect to its identity, quality, durability, reliability, safety or performance, such as malfunction, misuse or use error and inadequate labeling.

#### **14.1.4 Serious Adverse Event (SAE)**

Adverse event that,

- led to death,
- led to serious deterioration in the health of the subject, that either resulted in
  - a life-threatening illness or injury, or
  - a permanent impairment of a body structure or a body function, or
  - in-patient or prolonged hospitalization, or
  - medical or surgical intervention to prevent life-threatening illness or injury or permanent impairment to a body structure or a body function,
- led to foetal distress, foetal death or a congenital abnormality or birth defect.

Planned hospitalization for a pre-existing condition, or a procedure required by the clinical investigation plan (CIP), without serious deterioration in health, is not considered a serious adverse event.

#### **14.1.5 Serious Adverse Device Effect (SADE)**

Adverse device effect that has resulted in any of the consequences characteristic of a serious adverse event.

#### **14.1.6 Unanticipated Serious Adverse Device Effect (USADE)**

Serious adverse device effect, which by its nature, incidence, severity or outcome has not been identified in the current version of the risk analysis report.

Anticipated: an effect, which by its nature, incidence, severity or outcome has been previously identified in the risk analysis report. For relevant precautions applying to CMS008618 (ColdZyme® Mouth Spray), please refer to section 7.2.

#### **14.1.7 Incidents**

According to the Ordinance on Medical Devices Vigilance (MPSV), an incident is a malfunction, failure or a modification of the features or performance or an inaccurate label or instruction manual for a medical device, which directly or indirectly caused, may have caused in the past, or may cause in the future, death or a serious aggravation of the state of health of a patient, a user or another person.

### **14.2 DOCUMENTING AND REPORTING ADVERSE EVENTS, ADVERSE DEVICE EFFECTS AND DEVICE DEFICIENCIES**

#### **14.2.1 Documenting Adverse Events and Adverse Device Effects by the Investigator**

During all examinations, the investigator records any observed AEs and those reported by subjects upon questioning.

If an AE occurs, intensity (light=does not interfere with the subject's usual function, moderate=interferes to some extent with the subject's usual function, severe=interferes significantly with the subject's usual function), seriousness (if it is an SAE or not), relationship (not related, unlikely, possible, probable and causal relationship) to the IP, time of occurrence and duration of the observed AE, treatment and resolution/outcome will be recorded in the study documentation. All necessary measures are to be taken to determine the cause of the AE and its possible connection to the study.

#### **14.2.2 Documenting and Reporting Device Deficiencies and Incidents by the Investigator**

During all examinations after applying the investigational product, the subjects will be asked about any device deficiencies observed. If a device deficiency is reported, the deficiency including the assessment if it may be regarded as an incident will be recorded in the study documentation.

Reportable are all device deficiencies that might have led to a serious adverse event if

- a) suitable action had not been taken, or
- b) intervention had not been made or
- c) if circumstances had been less fortunate,

as well as any incidents.

The reporting is handled under the SAE reporting system and will be reported as specified in the form "Report on device deficiencies" (*"Bericht über Mangel des Medizinproduktes / Vorkommnis"*, in the ISF) immediately after becoming aware (not later than 3 calendar days) to the sponsor and the CRO.

**14.2.3 Reporting Serious Adverse Events by the Investigator**

All serious adverse events that occur for any reason during the study, will, even when the cause is not connected to the use of the device, be reported by the investigator as specified in the form "Report on serious adverse event" (*"Bericht über schwerwiegende unerwünschte Ereignisse"*, in the ISF) within 24 hours of awareness to the sponsor and the CRO.

**14.2.4 Safety Evaluation and Reporting by the Sponsor**

The sponsor is responsible for the ongoing safety evaluation of the clinical investigation, reviewing of the device deficiencies, incidents and SAEs reported by the investigator and any further reporting to the Ethics Committee (EC) and the Competent Authority as appropriate

## 15 STATISTICS

The present clinical investigation is designed as a double-blind, randomized, parallel-group, placebo-controlled study to test the study hypothesis that treatment with CMS008618 is superior to placebo in the efficacy treatment of naturally occurring common cold.

The primary objective of the present clinical trial is to evaluate the illness-specific quality of life as assessed per AUC of the WURSS-21 QoL composite subscore during first 8 days of symptoms.

The statistical analyses will be confirmatory for the primary endpoint and the major secondary endpoints, and exploratory for all other secondary endpoints. All statistical testing will be performed two-sided. The confirmatory significance level is fixed to a type I error rate  $\alpha$  of 5% (two-sided).

Statistical analysis will be done by the sponsor or under the authority of the sponsor. A general description of the statistical methods to be used to analyze the efficacy and safety data is outlined below. Specific details will be provided in the Statistical Analysis Plan (SAP).

### 15.1 STATISTICAL HYPOTHESES

A lower value of the primary endpoint (i.e., AUC of WURSS-21 QoL composite subscore assessed during first 8 days of symptoms) corresponds to fewer complaints, a higher value corresponds to more complaints. The study is aiming to show superiority of CMS008618 compared to placebo, i.e. aiming at lower values of the AUC values in the verum group compared to the placebo group.

The null hypothesis  $H_0$  and the alternative hypothesis  $H_A$  for the confirmatory analysis of the primary endpoint are formulated as follows:

- $H_0$ :  $\mu_{\text{verum}} = \mu_{\text{placebo}}$ , i.e. no difference between verum and placebo with respect to the primary endpoint.
- $H_A$ :  $\mu_{\text{verum}} \neq \mu_{\text{placebo}}$ , i.e. difference between verum and placebo with respect to the primary endpoint.

The null hypotheses  $H_0$  and the alternative hypotheses  $H_A$  for the major secondary endpoints are formulated analogously.

### 15.2 SIGNIFICANCE LEVEL

The confirmatory type I error rate for the study is set to 0.05 (two-sided). Due to the testing of a-priori ordered hypotheses, no multiplicity correction is considered necessary (Points to consider on multiplicity issues in clinical trials, CPMP/EWP/908/99, 2002).

### 15.3 SAMPLE SIZE CALCULATION

The sample size for the present study is calculated so that the comparison of the verum treatment group and the placebo treatment group for the primary endpoint has 90% power to detect a relevant clinical effect size  $\delta$  (i.e., the ratio of the absolute val-

ue of the difference between two means and the standard deviation) with a two-sided significance level  $\alpha=0.05$  as outlined below.

Based on the results of a previously conducted trial with the same IP in a comparable setting (sponsor's data on file), the difference between the verum group and the placebo group regarding the mean AUC of the WURSS-21 QoL composite subscore during first 8 days of symptoms is expected to be at least 33.900. The associated common standard deviation  $\sigma$  is expected to be 92.700. Therefore, the relevant clinical effect size  $\delta = |\mu_{\text{verum}} - \mu_{\text{placebo}}| / \sigma$  (i.e. the ratio of the difference between verum and placebo and the standard deviation) which should be detected with adequate power is assumed to be 0.366. This corresponds to  $p_1 = P(X < Y) = 0.602$  which is the probability that an observation, X, in group 1 will be less than an observation Y in group 2 when the alternative hypothesis is true. The null hypothesis being tested is that  $p_1 = 0.5$ .

Under these assumptions, a sample size of  $n = 169$  subjects in each treatment group will have 90% power to detect a probability of 0.602 that an observation in the verum group is less than an observation in the placebo group using a Wilcoxon (Mann-Whitney) rank-sum test with a 0.05 two-sided significance level (nQuery Advisor® Release 7.0).

Based on the sample size in the study and taking into account an assumption for a power of 80%, an effect size of 0.315 with regard to the main secondary endpoints (Jackson score AUC and exposure to relevant concomitant medication) would be detectable (with a power of 80% and a sample size of  $n = 169$  subjects in each treatment group,  $p_1 = P(X < Y) = 0.588$  is calculated, corresponding to an effect size  $d = 0.315$ .)

Thus, considering the planned 1:1 randomization with two treatment groups,  $n = 338$  subjects (with  $n = 169$  subjects per treatment group) are required for the primary confirmatory statistical analysis of the study.

Of all subjects originally randomized in a 1:1 manner, only those having the specified symptoms (see section 11.3) will actually start using the IP. Therefore, it is rather probable that the ratio of subjects actually having used IP and completing the study may differ from the original 1:1 ratio. In order to ensure the minimal number of required subjects per study group, 18% of additional subjects completing V2 and V3 are envisaged, resulting in the total number of 400 treated subjects.

